#### **14. The establishment and maintenance of investigational drug code, the method of unblinding, and the rule of unblinding in the event of an emergency**

Not applicable.

#### **15. Statistical analysis plan, definition and selection of statistical analysis data set**

##### **15.1 Definition and selection of analysis data set**

Enrolled Patients Set (EPS): defined as all enrolled cases, with or without investigational drug. The data set is used to analyze data such as demography and baseline information, subject allocation, and protocol violation.

Safety Analysis Set (SAS): defined as all enrolled cases that use the investigational drug at least once. The data set is used to analyze safety data.

Efficacy Evaluable Analysis Set (EEAS): defined as all enrolled cases who had at least one efficacy assessment after receiving investigational drug. The dataset is used for analysis of preliminary efficacy data.

Full Analysis Set (FAS): Defined as all enrolled cases who receive investigational drug at least once and have at least one post-baseline efficacy assessment according to the intention-to-treat (ITT) principle. The dataset is used for efficacy analysis.

Per-Protocol Set (PPS): defined as all cases, incorporated in the full analysis set, who comply with the protocol, have good medication adherence, do not use prohibited drugs during the trial, and have a defined efficacy assessment in the trial. The dataset is used for efficacy analysis.

Statistical analysis methods

## 15.2 Statistical analysis plan

Descriptive statistics are primarily used to analyze trial results. In general, measurement data will list the number of observational cases, mean, standard deviation, median, quartile, maximum and minimum. Enumeration data will list frequency and relative frequency. Unless otherwise specified, all of statistical tests will perform two-tailed test with a 95% confidence interval. Statistical analysis will be performed in a version of SAS 9.4 or higher version.

Use descriptive statistics to describe the number and proportion of subjects entering each analysis set, the number and proportion of subjects completing the trial and withdrawing consent, and the reasons for withdrawing consent (and proportion of subjects) for each dosage group; to describe the baseline characteristic of each dosage group.

Use the Safety Analysis Set to summarize treatment-emergent adverse event (TEAE) and adverse reaction for each dosage group; the AEs, occurs after signing informed consent and before treatment, will be only tabulated based on per subject and not summarized. TEAE is defined as the adverse event that is not present before dosing and occurs within 28 days (inclusive) after administration. The severity of adverse event and adverse reaction will be graded based on the NCI-CTCAE v5.0. Adverse event and adverse reaction will further be summarized based on System Organ Class and Preferred Term.

Using the safety analysis set baseline data, post-dosage data, and change from baseline were summarized for each follow-up visit and each dosage group, according to safety data such as laboratory, vital signs, electrocardiogram, physical examination, and otologic examination. Shift tables will be used to describe change from baseline after each follow-up visit to determine whether each examination result was normal and clinically significant as categorical data.

Use Per-Protocol Set to summarize efficacy data at each efficacy evaluation point and plot the efficacy-time curve of each subject, the mean efficacy-time curve of each dosage group, and the mean efficacy-curve of all subjects, according to efficacy data change from baseline in each dosage group.

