### 6.2.2 Steroids Prophylaxis

Dexamethasone intravenous infusion usage based on the body weight, starting on the -3 day and lasts until the 5th day of the post-operation, to reduce the postoperative inflammation and immune response to AAV medications.

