### **13.8 Expected adverse reaction and handling**

#### **13.8.1 Risk assessment of the trial**

Based on the clinical trial data from systemic administration of AAV drug, the risk of serious adverse events associated with AAV drugs includes hepatotoxicity (elevated liver enzymes, liver failure, etc.), thrombocytopenia, hemolysis, anemia, acute kidney injury, and neurotoxicity found on MRI. The local administration of AAV drug in the clinical trial such as ophthalmic trial gives rise to few systemic toxicity, mainly local inflammation at the site of administration and systemic reactions due to hormone administration at the same time.

Based on the data from drug administration by injected into inner ear of patients with profound

deafness in clinical trials, adverse reactions may be associated with AAV drugs, injection procedures, concomitant corticosteroids or a combination of these procedures and products. The most common adverse reactions (>5%) in the ear include mild hearing loss, dizziness, lightheadedness, nausea, and vestibular dysfunction, etc. Other adverse reactions with an incidence of less than 5% include otalgia, ear bleeding, unilateral deafness, tinnitus, taste change due to the injury of chorda tympani nerve, otitis media, perilymphatic fistula, reparative granuloma and tympanic membrane perforation, facial palsy, inner ear infection and meningitis, and sinusitis, etc. Systemic adverse events include hepatic impairment (elevation of ALT, AST, etc.), fatigue, food allergies, seasonal allergies, atopic dermatitis, urticaria, etc. These are systemic events that may be caused by systemic administration of corticosteroids and anesthetic reactions.

In summary, this clinical trial may be exposed to risks caused by the above-mentioned adverse reactions and risk control will be performed during the clinical trial to ensure the safety of the subjects.

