Nurse the subject carefully during the perioperative period of inner ear surgery; prevent infection with antibiotics and glucocorticoids after surgery. Contact the investigator promptly if subject fails to comply with medical advice or an accident occurs.

(7) Other toxic reactions: Symptomatic treatment is available. If blood tests and urine tests are abnormal, collect and detect samples again within 24 hours; and the corresponding treatment or therapy should be performed according to the test results.

(8) Risks associated with dexamethasone via intravenous injection:

Dexamethasone can reduce postoperative inflammation and decrease the immune response to AAV drugs, and is often used before and after ear surgery.

Common side effects of dexamethasone include increased appetite, stomach upset, nervousness, or restlessness. Less common but serious side effects include decreased or blurred vision, fluid retention, weight gain, increased blood sugar level, frequent urination, thirst, mood swings, confusion, and rash or urticaria. Other rare side effects include darkening or brightening of the skin, dizziness, facial flushing, hiccups, and increased sweating.

Dexamethasone may reduce resistance to the infection, which may lead to a sore throat, fever, sneezing or coughing.

Once side effects occur, discontinue dexamethasone immediately.

(9) General anesthesia:

Serious but very rare adverse events (negative side effects) associated with any types of anesthesia/surgery include seizures, coma, and death.

Rare but serious complications associated with general anesthesia include cardiac arrhythmias, increased or decreased blood pressure, transient high fever, rare reactions to drugs used in anesthesia, and airway obstruction.

The risk associated with a small amount of local anesthesia is low. Anesthetic injection is accompanied with a small risk of penetration of the eye or optic nerve, and the possibility of hemorrhage, which need to be treated if necessary.

(10) Risks associated with surgery:

1. Injury to ear ossicles such as injury to stapes, resulting in the dislocation of stapes; or even injury to oval window, leading to perilymphatic fistula.

2. Injury to jugular bulb, causing hemorrhage. In the event of hemorrhage, the ear canal should be filled with pressure to stop bleeding.

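### The adverse-event summary is anchored to dosing: events starting between Day -3 and the injection are only listed, worsening of pre-existing events is not counted, and a child given no vector is in no safety summary

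*Supplement*

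**What the plan says.** All references are to protocol version 5.0 in the Supplement.

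- **What is summarised.** Section 15.2: "Use the Safety Analysis Set to summarize treatment-emergent adverse event (TEAE) and adverse reaction for each dosage group".
- **What counts as a TEAE.** Section 15.2: "TEAE is defined as the adverse event that is not present before dosing and occurs within 28 days (inclusive) after administration". Worsening is not mentioned.
- **Earlier events.** Section 15.2 says that events after consent and before treatment "will be only tabulated based on per subject and not summarized". It defines neither dosing nor treatment for this purpose.
- **Safety population.** Section 15.1 gives the Safety Analysis Set as "defined as all enrolled cases that use the investigational drug at least once". The Enrolled Patients Set is assigned demography, baseline, allocation and protocol violations, not safety.
- **Steroid course.** Section 6.2.2 has intravenous dexamethasone "starting on the -3 day and lasts until the" fifth postoperative day.
- **Sources of harm.** Section 13.8.1 states that "adverse reactions may be associated with AAV drugs, injection procedures, concomitant corticosteroids or a combination of these procedures and products". The surgical risks in Section 13.8.2 begin with "Injury to ear ossicles such as injury to stapes, resulting in the dislocation of stapes".
- **Recording.** Section 13.5 records adverse events from consent onward. Section 13.1.1 defines an adverse event as one seen after use of a trial drug.

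**The concern.** Safety and tolerability are the primary purpose (Section 2.1). The vector is given only as part of a package: days of steroid, anesthesia, surgical access, then infusion. The protocol itself attributes possible reactions to any of these or to their combination. A summary whose clock starts at dosing leaves part of that package out because of when an event began, not what caused it.

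Three groups of events are affected: those that start before the injection, clinical events already present that become worse after it, and all events in a child who enters the regimen but never receives vector. With 4 to 12 cases planned, one child more or less in an incidence table is noticeable. Later trials are likely to take their expected rates from these tables rather than from a listing.

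**Working it through.** The plan derives no figure on this point, and the 4 to 12 cases in Section 5 have no stated derivation, so there is nothing to reproduce. The check is a comparison of rules, then a day count and one illustrative probability.

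**1. Tracing each kind of event through Section 15.2**

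| Event | TEAE? | Covered elsewhere? |
|---|---|---|
| Starts Day -3 to Day -1, under dexamethasone | No | Per-subject listing only |
| Starts during anesthesia or surgical access, before infusion | No if dosing means the infusion; unclear otherwise | Listing, if that counts as before treatment |
| Clinical event present before dosing, worse afterwards | No | Dose-limiting toxicity (DLT) only, if it reaches that grade |
| Laboratory, vital-sign, ECG, physical or otologic finding that worsens | Not needed | Change from baseline and shift tables |
| Steroid, anesthetic or surgical harm first seen after injection, within 28 days | Yes, whatever the cause | Not needed |
| Any event in a child given no vector | Outside the Safety Analysis Set | No safety summary |

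**2. Whether another summary closes the gap**

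- DLT is assessed over the 42 days after administration of RRG-003 (Section 3.1), so it has the same starting point.
- Adverse reactions are tied to administration of the drug (Section 13.1.3), with the safety data set as denominator (Section 13.3).
- Shift tables are confined to the Safety Analysis Set and to examination and laboratory findings.

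None of these counts a pre-injection clinical event.

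**3. The wording of the listing rule**

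If treatment means the vector, events from Day -3 to the injection are listed only. If it means the start of dexamethasone, those events fall outside the listing as described and are still not TEAEs. The gap exists on either reading.

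**4. Second injections**

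Section 3 allows two injections in the expansion, in both ears or repeated in one. Section 15.2 does not say which dose sets the clock. If it is the later one, an event that persists from the first injection and worsens after the second was present before dosing and is not a new TEAE.

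**5. Day count**

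The steroid course runs from Day -3 to Day +5, which is 9 days. Days -3, -2 and -1 precede Day 0: 3/9 = 33%. The other 6 fall on or after the injection day.

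**6. How likely an affected child is**

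The documents give no rate of pre-injection events, so the rate p per child is assumed and ranged, with children treated as independent. The chance of at least one affected child is 1 − (1 − p)^n.

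| Assumed p | n = 4 | n = 12 |
|---|---|---|
| 1% | 1 − 0.99^4 = 3.9% | 1 − 0.99^12 = 11.4% |
| 5% | 1 − 0.95^4 = 18.5% | 1 − 0.95^12 = 46.0% |
| 10% | 1 − 0.90^4 = 34.4% | 1 − 0.90^12 = 71.8% |

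These figures concern dosed children with an event starting before the injection. They do not cover worsening events or children who were never dosed.

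**The case against.** A reader might infer that harms from the steroid, anesthesia and surgery are excluded as a class. The documents do not support that. Section 13.1.1 counts an adverse event whatever its relation to treatment, so any such harm with onset after the injection and within 28 days is a TEAE. Facial palsy and taste change are watched for in postoperative care (Section 6.3) and would usually be counted.

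A reader might also infer that injuries during surgical access are certainly excluded. That holds only if dosing means the infusion. Section 9 describes the study as dosed by surgery, and Section 13.8.2 treats an accident in surgery and the injection as parts of one procedure. What stands here is that the term is undefined.

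The sponsor can add that:

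- pre-dose events remain visible, because a full listing for 4 to 12 children shows every one of them;
- serious events are reported regardless of cause (Section 13.6);
- worsening of measured findings is in the shift tables, and severe worsening can be a DLT, which is set by grade and does not require prior absence;
- a safety set tied to RRG-003 matches a purpose stated in terms of RRG-003 injection, and a partly completed injection still counts as use.

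All of this stands, and it narrows the point. It does not answer three things: steroid-period events are in no incidence table, worsening of a clinical event below DLT grade is counted nowhere, and a child who starts the regimen without receiving vector is in no safety summary. Section 4.3 foresees unsuccessful administration, so the last case is not fanciful.

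**Conclusion.** The concern holds in a limited form. Section 15.2 under-counts three groups: events with onset from Day -3 to the injection, clinical events that worsen after dosing, and events in children given no vector. Intra-operative events before infusion join the first group only if dosing means the infusion.

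The size cannot be stated from the documents. At an assumed rate of 1% to 10% per child, the chance that at least one dosed child is affected is about 4% to 34% with 4 children and 11% to 72% with 12.

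It would be tempting to say that each omitted event lowers an incidence by 17 to 33 percentage points (1/6 to 1/3). That presumes groups of three to six, that an event occurs, and that the child has no other counted event of the same kind. Under Section 3 the 30 µL group could hold a single child, and no event rate stands behind the figure, so it should not be used as an effect size.

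The change is worth making because safety is the primary purpose. The per-subject listing keeps it from being more serious.

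**What to change.** 1. In Section 15.2, define treatment-emergent events as those that are new, or that worsen in grade, from the first protocol-mandated intervention (dexamethasone, Day -3).
2. Show onset before and after vector infusion in separate columns, so that the vector-anchored count is kept. Define dosing and treatment, and state how the rule applies to a second injection.
3. Leave the Safety Analysis Set as it is for the RRG-003 analysis. Add a separate adverse-event summary for any child who started trial dexamethasone or surgery but received no vector.
4. Reconcile Section 13.1.1 (adverse event after use of the trial drug) with Section 13.5 (recording from consent).

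**Cost.** These are changes to analysis wording and touch no clinical rule. Section 13.5 already calls for recording from consent, with severity. The sponsor should check that the case report form captures a change of grade within an event, which that section does not spell out. The reported event rate will look slightly less favourable.

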### 3.1 Dose limiting toxicity (DLT)

Dose limiting toxicity (DLT) is evaluated within 42 days after administration of RRG-003 according to Common Terminology Criteria for Adverse Events, NCI-CTCAE V5.0. DLT is defined as hematologic toxicity  $\geq$  grade 4, nonhematologic toxicity  $\geq$  grade 3, or aural toxicity in grade 2 or 3 within 6 weeks. Aural toxicity was listed as follow:

| Adverse Events               | Grade 2 ear adverse events                                                                                  | Grade 3 ear adverse events                                                                              |
|------------------------------|-------------------------------------------------------------------------------------------------------------|---------------------------------------------------------------------------------------------------------|
| Ear pain                     | Moderate pain; limiting instrumental Activities of Daily Living (ADL)                                       | Severe pain; limiting self care ADL                                                                     |
| External ear pain            | Moderate pain; limiting instrumental ADL                                                                    | Severe pain; limiting self care ADL                                                                     |
| Hearing impaired (Pediatric) | Pediatric (on a 1, 2, 3, 4, 6, and 8 kHz audiogram):
Threshold shift >20 dB at 4 kHz in at least one ear | Pediatric (on a 1, 2, 3, 4, 6, and 8 kHz audiogram):
Hearing loss sufficient to indicate therapeutic |

|                                                |                                                                                                                                 |                                                                                                                                                                                                         |
|------------------------------------------------|---------------------------------------------------------------------------------------------------------------------------------|---------------------------------------------------------------------------------------------------------------------------------------------------------------------------------------------------------|

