#### 4. Subject inclusion criteria, exclusion criteria, and suspension criteria

##### 4.1 Inclusion Criteria

8. Participants and their guardians can fully understand and voluntarily sign the informed consent of this study, willing to cooperate with follow-up at the specified time points in the trial.
9. Be able to communicate well with the researchers and comply with the requirements under the help of the guardian. For young children without mature language skills, they could cooperate and comply with the requirements under the help of guardians.
10. A proper understanding of the trial and an appropriate expectation of the benefit.
11. 1-18 years old, gender is not limited.
12. A diagnosis of DFNB9 congenital deafness was determined based on the clinical symptoms, and gene mutation analysis for the presence of either *OTOF* homozygous or bi-allelic mutations in *OTOF*.
13. Audiology inclusion criteria: Severe to complete hearing loss ( $\geq 65$  dB).
14. Satisfy the requirements for otological surgery: conditions such as middle-inner ear deformity, vestibular-cochlear nerve development abnormality, and ear inflammation, etc. are excluded through CT scan and/or MRI scan within 3 months or during screening.

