## **11. Efficacy assessment criteria, including methods for evaluating parameters, observation time, recording and analysis**

Focusing on the purpose of the study, involving the efficacy assessment must have evaluation indicators or observation indicators, including primary and secondary evaluation indicators. At the same time, corresponding evaluation standards should be established for these indicators.

**Primary indicators:** tolerability (dose-limiting toxicity, DLT) at week 6.

**Secondary indicators:** safety, preliminary efficacy.

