### 13.5 Recording of adverse event

Serious adverse event occurring after acquirement of Informed Consent Form and before the end of the trial; all adverse events need to be recorded in the corresponding section of the CRF after acquirement of Informed Consent Form until subject out, regardless of whether the adverse event is related to the investigational drug, unless the subject withdraws the informed consent and follow-up visit cannot be performed.

All adverse events should be recorded in concise medical terms include: ① a description of adverse event and all associated symptoms; ② the time of occurrence and the duration of adverse event; ③ the severity of the adverse event; ④ the examinations and treatments performed due to the adverse event; ⑤ the final outcome of adverse event; ⑥ judge whether the adverse event was related to the investigational drug (if it could be judged).

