## 20. Expected progress and completion date of clinical trial

During the observation period of the administration, the subject is hospitalized on Day 1-Day 7 and undergoes physical examination, laboratory test, and otologic examination according to the trial flow chart during the follow-up visit on W2, W4, W6, W13, W26, and W52. Safety, tolerability, and adverse events are evaluated on Days 1, Day 2, Day 3, W1, W2, W4, and W6; long-term safety and preliminary efficacy are evaluated on W13, W26 and W52.

|                       |       |       |       |      |      |      |      |      |      |      |      |    |    |    |     |     |     |
|-----------------------|-------|-------|-------|------|------|------|------|------|------|------|------|----|----|----|-----|-----|-----|
| Pre administration    |       |       |       |      |      |      |      |      |      |      |      |    |    |    |     |     |     |
| RRG003 administration |       |       |       |      |      |      |      |      |      |      |      |    |    |    |     |     |     |
| Screening period      | Day-3 | Day 2 | Day-1 | Day0 | Day1 | Day2 | Day3 | Day4 | Day5 | Day6 | Day7 | W2 | W4 | W6 | W13 | W26 | W52 |
| Blood collection      |       |       |       |      |      |      |      |      |      |      |      |    |    |    |     |     |     |
| Hospitalization       |       |       |       |      |      |      |      |      |      |      |      |    |    |    |     |     |     |
| follow-up             |       |       |       |      |      |      |      |      |      |      |      |    |    |    |     |     |     |

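### The 28-day, new-events-only TEAE definition is shorter than the 42-day DLT window and the 52-week safety follow-up, so late events judged unrelated, including a DLT, have no assured summary

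*Supplement*

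**What the plan says.** All references are to protocol version 5 in the Supplement.

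- **TEAE definition (Section 15.2).** A TEAE is "the adverse event that is not present before dosing and occurs within 28 days (inclusive) after administration". No clause covers an existing condition that gets worse.
- **AE summaries (Section 15.2).** The instruction is: "Use the Safety Analysis Set to summarize treatment-emergent adverse event (TEAE) and adverse reaction for each dosage group". A later sentence in the same paragraph asks for a breakdown of adverse events and adverse reactions by System Organ Class and Preferred Term (SOC/PT), with no time limit. Laboratory, vital-sign, ECG, physical and otologic data are summarised at each visit as change from baseline, with shift tables.
- **DLT window (Section 3.1).** "Dose limiting toxicity (DLT) is evaluated within 42 days after administration of RRG-003". A grade 2 hearing item is "Threshold shift >20 dB at 4 kHz in at least one ear".
- **Primary indicator (Section 11).** "tolerability (dose-limiting toxicity, DLT) at week 6".
- **AE recording (Section 13.5).** "all adverse events need to be recorded in the corresponding section of the CRF after acquirement of Informed Consent Form until subject out".
- **Follow-up (Section 20).** "long-term safety and preliminary efficacy are evaluated on W13, W26 and W52".
- **Population (Section 4.1).** "Audiology inclusion criteria: Severe to complete hearing loss", with a threshold of 65 dB or more.

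**The concern.** Safety and tolerability are the primary purpose (Section 2.1), and the TEAE table is the main display of AEs. Its window closes two weeks before the primary indicator is read. A child could have a DLT on Day 35 that affects escalation under Section 3 and yet have no entry in the TEAE table.

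Every child also enters with the condition whose worsening is a DLT item. A definition restricted to events absent before dosing leaves it unclear whether a further loss of hearing counts as a TEAE.

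At stake is whether the safety tables can be reconciled with the dose decisions, and whether late events after a gene therapy are fully reported.

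**Working it through.** **Windows**

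- DLT window: 6 weeks × 7 = 42 days, which agrees with the plan's own two statements (Sections 3.1 and 11).
- Outside the TEAE window but inside the DLT window: 42 − 28 = 14 days; 14/42 = 33.3%.
- Follow-up to Week 52: 52 × 7 = 364 days. Outside the TEAE window: 364 − 28 = 336 days; 336/364 = 92.3%. This takes a single administration.
- Section 20 lists Week 6 as an AE evaluation, which is after Day 28. The schedule in Section 7 allows the Week 4 visit 5 extra days, so it can fall on Day 28 + 5 = 33.

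**Where each kind of event would appear under Section 15.2**

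| Event | TEAE table | Adverse-reaction table | Other |
|---|---|---|---|
| New, Days 1–28 | Yes | If at least possibly related | – |
| New, after Day 28, at least possibly related | No | Yes, no time limit | – |
| New, after Day 28, unlikely related or unrelated (including a DLT on Days 29–42) | No | No | SOC/PT only on a broad reading |
| Worsened hearing, any time | No, read literally | If at least possibly related | Per-visit otologic summaries |

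The third row is the gap. Section 13.3 counts as adverse reactions only events judged definitely, probably or possibly related. Section 3.1 defines a DLT by type and grade within 6 weeks and states no causality condition. Section 15.2 does not mention DLT.

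In the fourth row, a shift table that classes results as normal or clinically significant may show abnormal to abnormal, since every child starts at 65 dB or worse. Change-from-baseline summaries can show the deterioration, but not as a graded AE or a DLT.

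**From days to events (assumed values only)**

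The plan gives no onset times. With exponential onset of mean m, the share of DLT-window events after Day 28 is [F(42) − F(28)] / F(42), where F(t) = 1 − exp(−t/m):

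- m = 7 days: 1.6%
- m = 14 days: 9.0%
- m = 28 days: 18.6%
- uniform onset: 33.3%

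With uniform onset and an assumed per-child risk p over 42 days, the chance of at least one event on Days 29–42 is 1 − (1 − p/3)^n:

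- n = 4: 12.7% (p = 0.1) to 34.4% (p = 0.3)
- n = 12: 33.4% (p = 0.1) to 71.8% (p = 0.3)

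Uniform onset is the least favourable of the four patterns; earlier onset lowers these chances.

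**Weight of one event.** Section 5 plans 4 to 12 effective cases: 1/12 = 8% and 1/4 = 25%.

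**The case against.** The strongest defence is that little is actually lost. The 28-day limit is written for TEAEs alone. Adverse reactions are summarised by dosage group with no time limit, and the SOC/PT sentence refers to adverse events, not TEAEs. DLT is assessed separately to Day 42 and does not depend on TEAE status, and the general rule that categorical data are given as frequencies could cover DLT counts. All AEs are recorded and followed up, so nothing is missing from the database.

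Much of this stands, and it rules out three stronger readings that a reader might infer:

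- **All toxicity after Day 28 goes unreported.** Not supported. Late events judged at least possibly related belong in the adverse-reaction summary.
- **Worsening of hearing is expressly excluded.** Not supported. The definition is silent on worsening. A post-dose threshold shift could be coded as a new event, and it would show in the otologic change-from-baseline summaries.
- **A third of DLT-window events, or 92% of all events, are lost.** Not supported. These are shares of days; the shares of events are unknown.

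The defence does not close the remaining gap. The adverse-reaction route depends on a causality judgement in an open-label, single-arm trial. The word toxicity might be taken to imply attribution to the drug, but Section 3.1 does not say so. The SOC/PT sentence can be read as continuing the TEAE paragraph, in which case it adds nothing; read broadly, its scope differs from the TEAE table. A general rule on frequencies does not set a numerator, denominator or cohort for the primary indicator.

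**Conclusion.** The point holds in this limited form. As written, the TEAE tables omit new events from Day 29 on, including the last 14 of 42 DLT days, and on a literal reading they omit worsened hearing. The events with no assured summary are late ones judged unlikely related or unrelated, and a DLT can be among them. No DLT table is specified to make up for this.

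The fault is in definition and tabulation, not in data collection. Its size in events cannot be derived from the documents; the illustrative shares of 1.6% to 33% rest on assumed onset patterns. The conclusion assumes that Section 15.2 is followed as written. It also takes one administration: version 5 allows a second injection, and the SAP does not say whether the 28 days restart.

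Because the rule bears on the primary safety outcome in a very small trial and is cheap to mend, it should be corrected before the safety tables are produced.

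**What to change.** In Section 15.2:

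1. Define a TEAE as any AE that starts, or worsens from its pre-dose state, between the first RRG-003 administration and the last study visit.
2. State how the window runs, and to which administration an event is assigned, after a second injection.
3. Show TEAEs separately for the 42-day DLT window and for the time after it.
4. Apply the same definition to the SOC/PT summary.
5. Add a table of DLTs by dose cohort: number with a DLT over number evaluable.

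The data are already collected, so the cost is SAP wording and table shells. Reported AE counts will be somewhat higher, since unrelated and late events now enter the table; the split at Day 42 keeps them distinguishable.
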